## Abstract

**Background:**

Individual-level concomitance of infectious diseases and noncommunicable diseases (NCDs) is poorly studied, despite the reality of this dual disease burden for many low- and middle-income countries (LMICs).

**Objective:**

This study protocol describes the implementation of a cohort and biobank aiming for a better understanding of interrelation of helminth and Plasmodium infections with NCD phenotypes like metabolic syndrome, hypertension, and diabetes.

**Methods:**

A baseline cross-sectional population-based survey was conducted over one year, in the Taabo health and demographic surveillance system (HDSS) in south-central Côte d’Ivoire. We randomly identified 1020 consenting participants aged ≥18 years in three communities (Taabo-Cité, Amani-Ménou, and Tokohiri) reflecting varying stages of epidemiological transition. Participants underwent health examinations consisting of NCD phenotyping (anthropometry, blood pressure, renal function, glycemia, and lipids) and infectious disease testing (infections with soil-transmitted helminths, schistosomes, and Plasmodium). Individuals identified to have elevated blood pressure, glucose, lipids, or with infections were referred to the central/national health center for diagnostic confirmation and treatment. Aliquots of urine, stool, and venous blood were stored in a biobank for future exposome/phenome research. In-person interviews on sociodemographic attributes, risk factors for infectious diseases and NCDs, medication, vaccinations, and health care were also conducted. Appropriate statistical techniques will be applied in exploring the concomitance of infectious diseases and NCDs and their determinants. Participants’ consent for follow-up contact was obtained.

**Results:**

Key results from this baseline study, which will be published in peer-reviewed literature, will provide information on the prevalence and co-occurrence of infectious diseases, NCDs, and their risk factors. The Taabo HDSS consists of rural and somewhat more urbanized areas, allowing for comparative studies at different levels of epidemiological transition. An HDSS setting is ideal as a basis for longitudinal studies since their sustainable field work teams hold close contact with the local population.

**Conclusions:**

The collaboration between research institutions, public health organizations, health care providers, and staff from the Taabo HDSS in this study assures that the synthesized evidence will feed into health policy towards integrated infectious disease-NCD management. The preparation of health systems for the dual burden of disease is pressing in low- and middle-income countries. The established biobank will strengthen the local research capacity and offer opportunities for biomarker studies to deepen the understanding of the cross-talk between infectious diseases and NCDs.

**Trial Registration:**

International Standard Randomized Controlled Trials Number (ISRCTN): 87099939; http://www.isrctn.com/ISRCTN87099939 (Archived by WebCite at http://www.webcitation.org/6uLEs1EsX)

## Introduction

There is an alarming increase in the prevalence of noncommunicable diseases (NCDs) in low- and middle-income countries (LMICs). Although this is generally considered the result of an increase in life expectancy and westernization of lifestyle, these common and widely accepted NCD risk factors do not provide a complete picture [1]. In fact, within high-income countries, the risk of cardiovascular disease among migrants from LMICs remains elevated [2,3]. A relevant component of NCD may be attributed to infection/inflammation and neglected tropical diseases (NTDs), which, despite the epidemiological transition, remain high in LMICs, particularly in their neglected populations [4]. For Côte d’Ivoire, the 2010 Global Burden of Disease study showed both infectious diseases (IDs) and NCDs to be key drivers of morbidity and mortality [5]. On one hand, ID morbidity and mortality rates remain high, especially in the most vulnerable communities. On the other hand, there is a high prevalence of NCD risk factors, as evidenced already by the 2005 population-based World Health Organization Steps study in Abidjan and surroundings [6]. In the Taabo health and demographic surveillance system (HDSS) for routine monitoring of vital statistics in south-central Côte d’Ivoire, NCDs were the main cause in 20% of the deaths, which were mostly of cardiovascular origin, while IDs remained the primary cause of death [7].

### Inflammation and Cardiometabolic Phenotypes

Cardiovascular disease and diabetes mellitus contribute significantly to the disease burden in LMICs. They are also of particular interest with potential links to infections, as they are associated with altered immune and inflammatory responses [8]. Cardiovascular disease, diabetes, and their preclinical phenotypes (eg, atherosclerosis and metabolic syndrome) as well as their causal risk factors (eg, obesity, smoking, and air pollution) are associated with inflammation. Systemic low-grade inflammation promotes insulin resistance and atherosclerotic plaque formation. Barker formulated the hypothesis of the childhood origin of chronic age-related conditions [9], and in fact, inflammation is already associated with carotid intima media thickness and insulin resistance in children and adolescents [10]. For populations in LMICs, the link of cardiovascular disease and diabetes with inflammation implies that individuals surviving lethal IDs by mounting a strong inflammatory response may become more susceptible to age-related inflammatory phenotypes later in life [3,11-13]. In addition, repeated and chronic infections may lead to subtle cell and organ damage and permanent derailment of the immune system, which could enhance susceptibility to NCD risk factors later in life. In fact, a significant proportion of the disability-adjusted life years attributed to cardiovascular disease in LMICs is related to inflammation precursors, such as rheumatic fever and other NTDs [4]. The role of infections as risk factors for diabetes remains poorly understood [14] even though it is thought that diabetes puts patients at higher risk for infections that are prevalent in LMICs [8,15]. Thus, there is an overall lack of adequate data to determine the true extent of cardiovascular disease and diabetes that result from or are prevented by infections in LMICs.

### Helminth Infections and Cardiometabolic Phenotypes

Helminth infections contribute substantially to the NTD-associated global burden of disease, and several are highly prevalent in many parts of the world [16]. Soil-transmitted helminths and schistosomes are among the most prevalent infections in human populations in LMICs [17]. The contribution of helminths to NCD is the focus of intense research [18-21]. Individuals with heavy and chronic helminthic infections can suffer from malnutrition, stunted growth, anemia, and cognitive impairments, which may have a direct impact on NCD risk or an indirect impact through lifestyle measures [22]. Several animal models show a beneficial influence of helminth infections on metabolic homeostasis [19,23]. Cross-sectional epidemiological studies showed an inverse relationship between diabetes and lymphatic filariasis [24,25]. Infection with soil-transmitted helminths was associated with lower insulin resistance and lipid levels [26]. While studies on schistosomiases and strongyloidiasis reported negative association with glucose tolerance [27,28], other studies reported a beneficial effect, and even lower prevalence of diabetes in association with *Schistosoma japonicum* [29]. A study of Australian Aboriginal adults revealed a strong inverse relationship between infection with *Strongyloides stercoralis* and type 2 diabetes [30]. Epidemiological evidence on helminths and hypertension is very limited. A study among schoolchildren in Uganda found helminth infections to be positively associated with blood pressure [31]. Generally, helminth infections are clinically asymptomatic, but their direct and indirect effects on the host’s immune system might be of particular relevance to the host’s susceptibility to NCDs. The NCD risk may further depend on the host-pathogen relationship based on their co-evolved genetic variation. Endemic helminth infections likely exerted a strong selective pressure contributing to specific genetic host factors conferring an altered risk for immune-mediated diseases [32].

### Malaria and Cardiometabolic Phenotypes

Malaria still ranks highest on the Global Burden of Disease list for many African countries, including Côte d’Ivoire [5]. In the first 3 years of running the Taabo HDSS, malaria contributed to 20% of all registered deaths, ranking as the number one cause of death [7,33]. Although fever, a common symptom of malaria, can go along with stress-induced hyperglycemia [34,35], there is a lack of epidemiological evidence on the association of malaria with parameters of the metabolic syndrome or diabetes. According to clinical studies, malaria, even in the uncomplicated form, led to altered lipid profiles, which in some cases were prolonged, despite malaria treatment [36]. The malaria-related changes in lipid profiles have not been studied for their potential role in atherosclerosis and hypertension. A higher prevalence of *Plasmodium falciparum* infection was found among persons with diabetes [37]. In addition, fasting glucose, glycosylated hemoglobin (HbA1c), and insulin resistance were higher among non-diabetic persons with malaria [38]. Maternal malaria has also been demonstrated to have an impact on blood pressure and glucose in the offspring, thereby increasing the risk of developing hypertension and diabetes later in life [9]. Recent evidence from the African Genome Variation Project demonstrated that genetic loci under positive selection in individuals of African compared to European descent were related to malaria susceptibility on one hand (*CR1*) and osmoregulation and hypertension (*ATP1A1* and *AQP2*) on the other hand [39]. Interestingly, preliminary evidence suggests that variation in *CR1* may be related to coronary artery disease and hypertension [40]. Individuals of African descent have higher levels of circulating angiotensin-II due to its protective effects on malaria, thus genetic positive selection of the variants in the renin-angiotensin-aldosterone system may have been driven by malaria [41]. African-Americans have a higher prevalence of hypertension than Caucasians living in the same settings [42]. Hence, it has been hypothesized that persons with ethnic origins from malaria-endemic regions may be more susceptible to hypertension (due to co-evolution and positive selection of protective genetic variants).

### Relevance Health and Demographic Surveillance System With Integrated Biobanks

A complex array of different infection, environment, host lifestyle, and genome interactions are expected to drive immunological and inflammatory diseases, necessitating individual-level complex data to disentangle these disease networks. Hence, there is a pressing need to better understand the links between IDs and NCDs, to enable the development of integrated approaches for intervention against this dual disease burden. In LMICs where vital statistics and setting-specific health information are scarce, HDSS is recognized as a powerful platform for assessing and longitudinally monitoring key demographic parameters and disease burden [43,44]. Moreover, HDSS provides a unique means for population-based epidemiological and health systems research, and evidence collected in the context of HDSS effectively feeds into policy [44,45].

The integration of biomarkers into research protocols are of relevance to assign causality to observed associations, improve mechanistic understanding of diseases, and identify novel targets for disease screening, diagnosis, treatment, and surveillance. The availability of broad “-omics” analyses of biospecimens allows for systemic approaches (including systems medicine and exposome research) that will strengthen the investigation of disease mechanisms and considerably improve the understanding of disease mechanisms [46,47]. Applying the “meet-in-the-middle paradigm”, linking biomarkers to both exposures and health outcomes—or in the case of this project to both IDs and NCDs—will allow the investigation of biomarkers likely to play a role in the causal pathway from exposure to disease (Figure 1). Therefore, this methodological approach of meet-in-the-middle is of potential relevance for identifying preventive and therapeutic targets [48,49]. Venous blood (suitable for cytokine profile, DNA extraction, and subsequent methylation profile typing) [50], urine (suitable for metabolomics profile detection) [51], and stool samples (suitable for gut microbiome typing) [52,53] constitute common biospecimens applied towards biomarker assays in disease mechanistic linkage. Novel protocols for biospecimen sampling, processing, and storage are essential for the establishment of high-quality biobanks in remote areas of LMICs in the context of dual disease burden research.

**Figure 1 figure1:**
[figure not shown]
Framework of the CoDuBu study (IDs: infectious diseases; NCDs: noncommunicable diseases; M-i-M: meet-in-the-middle paradigm).

### Objectives of the CoDuBu Study

The overarching goal of this project is to deepen our understanding of the dual burden of IDs (helminthiases and malaria) and NCDs (hypertension and diabetes) among adults in the Taabo HDSS in south-central Côte d’Ivoire, to set the stage for future mechanistic research, and to translate key findings into policy action. We will pursue the following specific objectives:

To conduct a population-based cross-sectional survey in adults from rural and semi-urban parts of the Taabo subdistrict to assess (a) the prevalence, intensity, and distribution of helminth (*Ascaris lumbricoides*, *S. stercoralis*, hookworm, *Trichuris trichiura*, *Schistosoma haematobium,* and *Schistosoma mansoni*) and *Plasmodium* infections, (b) the prevalence and distribution of metabolic syndrome, hypertension, and diabetes, and (c) the co-occurrence of these IDs and NCDs and the distribution of these comorbidities and their respective risk factors at the level of individuals.To establish a biobank consisting of blood, urine, and stool as an investment for future longitudinal biomarker research on the mechanistic link between helminth and *Plasmodium* infections, and hypertension and diabetes.To prepare the local health system for the uptake and management of NCDs through assessment of deficiencies and provision of necessary training, instruments, and facilities to the local health staff and health centers.

## Methods

### Location

The study was conducted in the Taabo HDSS, which is located about 150 km north-west of Abidjan, in the Agneby-Tiassa region of south-central Côte d’Ivoire. The Taabo HDSS covers a surface area of about 980 km^2^and includes an urban setting (Taabo-Cité), 13 villages, and more than 100 small hamlets [33]. The Taabo HDSS was set up in 2008 and has been operational since 2009. It collects longitudinal demographic data at the individual and household level, usually done in three rounds per year [33,54]. The 2012 demographic information of the Taabo HDSS has been published elsewhere [33]. In brief, crude birth and mortality rates were 33.9 and 8.2 per 1000 population. In- and out-migration rates were 136.9 and 160.1 per 1000 population respectively, with a population growth rate of 2.5 per 1000 population. Male to female ratio was 104:100, and total fertility rate was 4.8 children per woman. Life expectancy was 61 years for males and 65 years for females. Main disease patterns include malaria and NTDs [33]. Deaths are usually reported by key informants, and verbal autopsies are conducted using standard protocols to determine causes of death [7,33]. Main causes of death include malaria, HIV/AIDS, and tuberculosis [7]. Specific in-depth questionnaire and epidemiological surveys have previously been carried out on subsamples of the population to deepen the understanding of malaria, NTDs, and iron-deficiency anemia [54-58]. The HDSS population (approximately 42,000 individuals from 6700 households) is predominantly Ivorian, with Akan as the main ethnic group. There are eight health facilities in the Taabo HDSS area: a 12-bed hospital in Taabo-Cité and seven health centers and dispensaries across the 13 villages [33]. Figure 2 shows a map of the Taabo HDSS.

We selected three areas from the Taabo HDSS for the purposes of this study. Selection was based on degree of urbanization, potential to provide at least one adult per household towards reaching an effective sample size, prevalence of malaria and helminthiases from preliminary surveys, availability of health center for examination, proximity to the main hospital in Taabo-Cité for ease of referral, and higher potential for follow-up. We therefore selected Taabo-Cité, Amani-Ménou (40 km from Taabo-Cité in the south) and Tokohiri (36 km from Taabo-Cité in the north) reflecting semi-urban, rural, and very rural settings in the Taabo HDSS.

**Figure 2 figure2:**
[figure not shown]
Map of the Taabo HDSS, located in south-central Côte d’Ivoire. The sites of the CoDuBu baseline study were Taabo-Cite, Tokohiri (36 km north of Taabo-Cite) and Amani-Menou (40 km south of Taabo-Cite). (Figure is reused with permission from Oxford Academic Journals [33]).

### Preparation

For site preparation, the study team visited the district and village chiefs and informed them about the study. In addition, the hospital and health centers in the selected sites were visited for assessment of diagnostic and treatment capabilities for hypertension and diabetes and for malaria and helminthiases. Informing the local population about the study included information events planned by the HDSS staff, in collaboration with the CoDuBu study team. The HDSS field staff had 2-day training on performing interviews and instruction of participants on biospecimen collection. The medical team also underwent 2-day training on health examinations and laboratory screening. The study procedures were piloted on 10 local residents, who would not be participating in the main study.

### Design

This was a population-based cross-sectional study among adult participants aged ≥18 years, randomly sampled within the selected Taabo HDSS areas. The examinations and interviews were conducted between April and August 2017. A biobank was established for future biomarker research based on biospecimens collected from the participants. The survey occurred in two phases.

Phase I (health examination; April and May 2017) took place over 2 days for each participant. The first day included obtaining informed consent, provision of materials and instructions for biospecimen collection (clean plastic container and OMNIgene.GUT tube (DNA Genotek Inc) for stool and BD Vacutainer urine collection system (Beckton, Dickinson & Co) for urine, at participants’ residences. The next morning, while participants underwent health examinations (at the health center) in a fasting state, fresh morning stool and urine samples collected at home were transferred cooled (~4°C) to the Taabo-Cité central laboratory for immediate pre-analytic processing. In the field, health examinations included point-of-care glucose, hemoglobin, HbA1c, lipids tests, anthropometry (height, weight, neck, arm, waist, and hip circumference), blood pressure, pulse, temperature, as well as preparation of dried blood spots (DBS) on filter papers. At the end of the examination, blood sample (stored at 4°C within 10 minutes of venepuncture) and DBS were sent to the laboratory for further processing. Multimedia Appendix 1 shows the detailed flow of the health examination in the field.

In the laboratory, blood samples were applied towards malaria diagnoses (rapid test and microscopy) and further aliquoted and stored (together with the DBS) in a -80°C biobank. Stool from the plastic container was analyzed for helminth eggs (or larvae), and urine was subjected to *S. mansoni* test and dipstick urinalysis (for blood, proteins, blood, glucose, urobilinogen, bilirubin, leucocytes, ketones, nitrites, pH, and specific gravity). Urine samples that tested positive for blood underwent a filtration method for *S. haematobium*. The remaining urine and OMNIgene.GUT-stabilized stool were aliquoted and transferred to the -80°C biobank. Case reporting and management of diagnosed IDs and NCDs were incorporated within the health examination period (Figure 3). Multimedia Appendix 2 shows the detailed flow of the laboratory work.

In Phase II (interview; June-August 2017), participants were interviewed on a third day, following health examinations. Interviews assessed among other factors, sociodemographic characteristics, health status, ID and NCD risk factors, medication and vaccination history, health care use, as well as knowledge and attitudes regarding NCDs.

Two study teams of about 10 persons each were responsible for the conduct of the study. The teams included 1 research staff (supervision of adherence to study protocol), 1 medical doctor (supervision of physical examination), 3 study nurses (conduct physical examination and point-of-care tests), 1 laboratory supervisor (supervision of work-up and analyses of biospecimens), 1-2 laboratory technicians (work-up and analyses of biospecimens), 2 HDSS field staff speaking the local language(s) and resident in the study area (informed consent, instruction for home biospecimen collection and health interviews), and 1 driver.

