### In-Person Interviews

The in-person interviews were done using a tablet-based questionnaire in Open Data Kit format [67], lasting between 45 and 60 minutes. Questions covered demographic factors (eg, age, sex), water supply and sanitation facilities (availability and use), know-how, attitude, and behavior towards tobacco smoking, physical activity, obesity, alcohol consumption, and nutrition. They also included environmental risks (eg, exposure to mosquito coils, pesticides, indoor biomass fuels), gender, hormonal and reproductive factors, psychosocial stressors and resilience to them, disease symptoms (respiratory, cardiovascular, and diabetes), family history of disease, medical diagnoses and treatments, vaccination history, and access to health care.

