### Health Systems Preparation and Diagnostic Follow-Up

At the end of the data collection for this baseline survey, participants were informed on IDs, NCDs, and their risk factors in order to promote healthy lifestyle. Information and education campaigns—through radio, posters, and flyers—were established for education of the population. Participating health centers were equipped with facilities for hypertension and diabetes screening, and the main hospital at Taabo-Cité was made a referral central center for initial NCD diagnosis and treatment in the area. Medical staff on the project were trained and certified for performing electrocardiography. Participants who were diagnosed with any screened infection were treated free of charge. Participants diagnosed with any NCD were followed up for confirmation. Transportation fees for confirmation and first month of treatment were covered by the study. Further management are being co-ordinated by study partners in Côte d’Ivoire, ensuring patient enrollment in a subsidized treatment plan.

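### Interviews followed the reporting and management of screening results, so self-reported diagnoses, treatment, behaviours and NCD knowledge are open to influence by the study itself, and the article states no safeguard

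*Protocol article*

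**What the plan says.** The Design section of the protocol article sets out two phases.

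- **Phase I:** "Phase I (health examination; April and May 2017) took place over 2 days for each participant". Within it, "Case reporting and management of diagnosed IDs and NCDs were incorporated within the health examination period".
- **Phase II**, dated June to August 2017: "participants were interviewed on a third day, following health examinations". The interview covered "health status, ID and NCD risk factors, medication and vaccination history, health care use, as well as knowledge and attitudes regarding NCDs". The In-Person Interviews section adds "family history of disease, medical diagnoses and treatments, vaccination history, and access to health care".

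The section on Health Systems Preparation and Diagnostic Follow-Up describes what happened to people with findings: "Participants who were diagnosed with any screened infection were treated free of charge". Those with an NCD finding were followed up for confirmation, and "Transportation fees for confirmation and first month of treatment were covered by the study". That section dates neither the treatment nor the confirmation visits.

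Textbox 1 lists the prevalence of doctor's diagnoses and treatments, access to care, NCD knowledge and NCD risk exposures as key interview phenotypes, and describes the interview variables as risk factors and effect modifiers. Data Analyses plans linear or logistic models of health outcomes on predictors. Neither Data Analyses nor Limitations mentions that the interview came after the results were known.

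**The concern.** A person first found to have a raised value in April, told of it and referred, could truthfully report a diagnosis and a treatment in July that the study itself had produced. Counted as baseline, such answers raise the prevalence of diagnosis, treatment and health care use above the level that existed before the survey.

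Behavioural items carry a second risk. People told of a condition may change their diet, smoking, drinking or activity, or may report them differently. Being told depends on the Phase I result, so any such shift is differential with respect to the outcome. When the behaviour is then used as a predictor of that outcome, the association can partly reflect reverse causation. Sampling weights and adjustment for other covariates do not remove this.

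**Working it through.** The article gives no figure on this point, so there is none to reproduce. The check has four parts.

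**1. Order and interval.** Inputs: the months stated in Design.

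- Shortest possible gap: 31 May to 1 June = 1 day.
- Longest possible gap: 1 April to 31 August = 152 days.

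A one-day gap needs an examination on the last day of May and an interview on the first day of June. For nearly everyone, the third day was therefore not the day after the examination. Design places case reporting and management inside the earlier window.

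**2. Which variables are exposed.**

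| Variable | Source and timing | Exposed? |
|---|---|---|
| Infections, glycaemia, lipids, blood pressure | Measured in Phase I | No |
| Hypertension | Defined from measured pressure alone (Physical Examination) | No |
| Sociodemographic and household data | Surveillance database, collected before the survey (Textbox 1, Data Analyses) | No |
| Family history, past vaccination | Interview, stable facts | Little |
| Diagnoses, treatment, medication, health care use | Interview | Yes |
| Modifiable risk behaviours | Interview | Yes |
| NCD knowledge | Interview; general education came only at the end of data collection | Yes, but less |

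Both sides of the infection-NCD co-occurrence aim (Objectives) are Phase I measurements.

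**3. How many would have had a finding to report.** Inputs from Sample Size Estimation: malaria 30%, diabetes 6%, independence, 1,020 participants.

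- P(malaria or diabetes) = 1 − (1 − 0.30)(1 − 0.06) = 1 − 0.70 × 0.94 = 0.342.
- 0.342 × 1,020 = 348.8, about 349 people.
- Malaria: 0.30 × 1,020 = 306. Diabetes: 0.06 × 1,020 = 61.2. Both: 0.30 × 0.06 × 1,020 = 18.4. Check: 306 + 61.2 − 18.4 = 348.8.
- Malaria share: 306 / 348.8 = 87.7%. Diabetes without malaria: 348.8 − 306 = 42.8, about 43 people.

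Helminth infections, hypertension and dyslipidaemia would enlarge the group. The sample size section gives no planning prevalence for them.

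**4. Direction for the diagnosis item.** Among people who screen positive for a condition, let t be the share already diagnosed before the study, and r the share of the others who report the study's finding as a diagnosis. The interview then shows t + (1 − t)r. The article gives neither value. The values below are assumptions that show the range only.

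| t | r = 0.25 | r = 0.50 | r = 1 |
|---|---|---|---|
| 0.20 | 0.40 | 0.60 | 1.00 |
| 0.40 | 0.55 | 0.70 | 1.00 |
| 0.60 | 0.70 | 0.80 | 1.00 |

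The shift is upward for any r above zero. It is zero if the questionnaire asks only about the time before the examination.

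**The case against.** The strongest reply is that this is a risk and not a demonstrated fault. The questionnaire and the detailed flow charts are not shown, and a journal article commonly leaves item reference periods to such documents. Nothing in the text says that diagnoses made by the study would be counted as pre-existing, and Data Analyses says that separate analysis plans will go to statistical review. This stands, and it limits the point to saying that the items are open to contamination with no safeguard stated.

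Four further replies also carry weight.

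- Design places management before the interviews only in general terms. How many people had actually started treatment by interview is unknown.
- The diagnosis item in Textbox 1 names HIV and tuberculosis, which the study did not test for and so could not have newly detected. The item is not confined to them, however.
- Most of the 34.2% is malaria, and it is not obvious why a malaria result would change reported smoking, diet or NCD knowledge. That mechanism is most plausible for people told of an NCD.
- Excluding or stratifying by notification would do harm. For a diabetes model, removing those notified of diabetes removes the roughly 61 expected cases. For continuous glucose or blood pressure, it truncates the outcome.

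None of this changes the order of events, which the article states itself. The end-of-survey timing of general education weakens the knowledge point without removing it, because individual results had been reported earlier.

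**Conclusion.** The concern holds for a defined set of items: doctor's diagnoses, treatment, medication, health care use, modifiable behaviours and, less strongly, NCD knowledge. These were asked 1 to 152 days after an examination phase that included reporting and managing cases, and the article states no rule for separating what existed before from what the study started.

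A reader might infer more, and the documents do not support it:

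- **That the baseline interview data as a whole are contaminated.** Stable items are hardly touched, and reference periods in the unseen questionnaire could protect others.
- **That the co-occurrence results or the measured disease prevalences are compromised.** They rest on Phase I measurements.
- **That 34.2% measures the bias.** It is the share expected to have a malaria or diabetes finding, given the planning prevalences and independence, and assuming every such finding was reported before interview. The size of any bias cannot be derived from the article.

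The point is modest in scope but cheap to settle. It matters most for the listed prevalence of diagnoses and treatments and for models with behaviours as predictors.

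**What to change.** Recruitment and interviews were complete by September 2017 (Results), so the order cannot change and the remedy is analytic. Add to Data Analyses:

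1. Count a diagnosis, treatment or medication as present at baseline only if it predates the participant's examination date. Establish this from interview dates, item reference periods and whatever case-reporting and referral records the study holds. Label the rest as newly detected by the study.
2. Report NCD knowledge, health care use and treatment prevalence by notification status, and give the distribution of the examination-to-interview interval.
3. For models with modifiable behaviours as predictors, do not exclude or stratify on notification of the outcome condition. Report a sensitivity analysis by examination-to-interview interval, and state possible reverse causation as a limitation. The interval analysis is only a partial check, because results may already have been known at the shortest intervals. If sites were visited in sequence, the interval may also be tied to site.

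The cost is some record linkage, one sensitivity analysis, and a group of participants whose diagnoses cannot be dated and who need their own category. The article does not describe the case-reporting records, so confirm first that they carry dates.
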